#### 2.5.2. Cost-effectiveness.

A cost-effectiveness model will be developed following ISPOR guidelines for trial-based economic evaluations [36]. The model will evaluate the potential economic value of the TP compared to standard care from a healthcare payer perspective. While a societal perspective may capture broader costs and consequences, such as productivity losses and informal care, it is not the primary perspective for decision-making in this context. The analysis will adopt a time horizon sufficient to capture all relevant costs and health outcomes associated with the intervention, extending beyond the trial follow-up period where necessary. Health outcomes will be expressed in terms of QALYs, integrating both quality and quantity of life, based on directly measured health state utilities obtained from the EQ-5D-5L utility scores. These intermediate outcomes will help capture potential longer-term benefits of the intervention beyond trial follow-up period. Costs will include healthcare resource use as well as the operational costs of implementing the TP. The primary outcome of the model will be the incremental cost-effectiveness ratio (ICER), expressed as the additional cost per QALY gained.

Future costs and health outcomes will be discounted in accordance with Belgian guidelines, applying a discount rate of 3% for costs and 1.5% for health effects [37]). Uncertainty in the ICER will be explored through both deterministic (one-way) sensitivity analyses and probabilistic sensitivity analysis. A cost-effectiveness acceptability curve will be generated to assess the probability of cost-effectiveness across a range of willingness-to-pay thresholds. In addition, value of information analyses, including the expected value of perfect information and expected value of partial perfect information, will be conducted to quantify decision uncertainty and inform the potential value of further research [38].

#### 2.5.3. Process evaluation.

Quantitative data (including enrolment registration forms, sociodemographic variables, and experience surveys) will be analysed using descriptive statistics. Information extracted from the individualized transition plans will be further examined through quantitative content analysis [39]. Interviews will be audiotaped and transcribed verbatim, and qualitative data will be analysed thematically using NVivo software [40]. All data sources will be systematically organized according to the stages of the transition process (i.e., pre, peri, and post) and key domains of interest (e.g., readiness, support, engagement). This structured framework allows quantitative and qualitative data to be directly linked, enabling triangulation and comparison across sources. Integrating data in this way ensures that findings from one method can contextualize and enrich those from another, providing a full and nuanced understanding of the programme’s impact.

### 2.6. Ethics approval

The study follows a multicentric design and has received ethical approval from the Ethical Committee of Antwerp University Hospital and Ghent University Hospital (reference number: B3002024000166), Belgium.

Written informed consent will be obtained from all participants, and assent will be sought from minors where applicable. Participants will be informed that refusal to participate, or withdrawal from the study at any time, will have no impact on their current or future care.

All data will be securely stored in de-identified form and will only be accessible to authorized project researchers via encrypted platforms with two-factor authentication. Data will be retained for a period of 20 years.

Study findings will be disseminated through peer-reviewed publications and presented at national and international conferences. In addition, a summary of the results will be shared with clinicians and policy makers through relevant local, national, and international networks and events.

## 3. Discussion

This study presents the protocol of a multicentric quasi-experimental study evaluating the COCCOS TP for AYAs with chronic conditions. By combining assessments of effectiveness, cost-effectiveness, and implementation, the study aims to generate insights on both outcomes and the delivery of a co-designed TP in real-world clinical settings, addressing the need for evidence-based transitional care.

A key strength of this study is its broad evaluation approach, addressing not only clinical but also economic and implementation outcomes [41]. While previous studies have shown potential benefits of structured TPs, such as improved adherence, self-management, and reduced healthcare utilization, evidence is often fragmented and limited to single outcomes or short-term effects [42–44]. By integrating measures of transition readiness, empowerment, treatment adherence, mental health, and health-related quality of life, this study calls for more comprehensive evaluations. The inclusion of a cost-effectiveness analysis is particularly relevant given increasing pressure on healthcare systems to allocate resources efficiently. Demonstrating the economic value of TPs is essential to support their long-term integration into routine care pathways. Another important strength is the participatory development of the intervention. The TP was co-designed with AYAs, families, and healthcare providers using EBCD methods, enhancing its relevance, acceptability, and feasibility [45]. Compared with top-down designed interventions, co-created programmes better align with patient needs and clinical practice realities, increasing uptake and facilitate implementation in practice [46,47]. However, long-term sustainability is likely to depend not only on co-creation but also on organizational and system-level support. The TP’s structured yet flexible design also allows adaptation to different disease trajectories and care contexts. This study further contributes to the literature by focusing on prevalent chronic conditions, addressing a gap in the literature that, although well-studied in type 1 diabetes, has been less explored for other common conditions and has often focussed on rare or highly specialized conditions [14]. Including multiple conditions enables assessment of whether the TP performs consistently across different clinical contexts and enhances the generalizability and scalability of findings. Given the feasibility nature of this study, findings should be interpreted with caution and are intended primarily to inform the design of a future larger-scale trial rather than to draw definitive conclusions on effectiveness [48,49].

Despite these strengths, several limitations should be acknowledged. First, the quasi-experimental design without randomization may introduce selection bias. To address this, IPTW will be used to balance observed covariates between groups, however, this approach does not account for unobserved confounders [50,51]. Second, the study relies on self-reported measures, which may introduce reporting bias and social desirability effects [52,53]. However, the use of validated instruments such as the TRAQ 6.0, GYPES, MARS-5, EQ-5D-5L, and HADS strengthens the reliability and comparability of findings [54]. In addition, the relatively short follow-up period of four months post-transfer may not fully capture long-term outcomes, such as sustained adherence, disease control, or healthcare utilization patterns [55]; nevertheless, it does fully cover transition’s most critical point of healthcare continuity, i.e., the transfer. The embedded process evaluation, however, will help interpret findings and identify barriers and facilitators. As transition is inherently a longitudinal process, future studies should include longer follow-up periods to evaluate the durability of effects. Due to time constrains within the current project, this was not feasible. Implementation across multiple centres and conditions may also introduce contextual variability, including differences in organizational structures, care practices, and resource availability [56]. While this heterogeneity may complicate interpretation findings, it is also a strength in terms of external validity. The embedded process evaluation will be crucial to understand how contextual factors influence implementation, identify barriers and facilitators, and explain observed outcomes.

Importantly, this study positions TPs within the broader framework of the sextuple aim of healthcare, aiming to improve patient outcomes and experiences, support healthcare providers, optimize costs, and indirectly promote health equity and environmental sustainability [57]. The inclusion of healthcare providers’ perspectives acknowledges that successful implementation depends not only on patient engagement but also on provider workload, interprofessional collaboration, and organizational support.

The findings of this study will have several implications. First, they will inform the refinement and optimization of the COCCOS TP, allowing adaptation of its components based on user feedback and real-world implementation insights. Second, the results will provide key parameters, such as recruitment rates, retention, variability in outcomes, and preliminary effect sizes, needed to design a future larger-scale evaluation study, such as a pragmatic trial or hybrid effectiveness-implementation study. Third, the economic evaluation will offer early evidence to inform policy and decision-making regarding the integration of transition programmes into routine care.

In conclusion, this study addresses critical gaps in the evaluation of transitional care by combining co-designed intervention development with a comprehensive mixed-methods feasibility assessment. By generating evidence on effectiveness, cost-effectiveness, and implementation, it contributes to the development of sustainable, patient-centred transition programmes for AYAs with chronic conditions. Ultimately, improving the healthcare transition from paediatric to adult care has the potential to enhance long-term health outcomes and reduce the burden on healthcare systems.

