#### 2.3.2. Participants.

The study will focus on three common chronic childhood-onset conditions: type 1 diabetes, asthma, and obesity. The three diagnostic groups will be included to ensure variability and representativeness. Eligibility criteria for the intervention group include: being 17 years old, having a diagnosis of one of the target conditions, at least one paediatric outpatient visit in the past 12 months, Dutch-speaking, and a planned transfer to adult care within 12 months. Participants in the control group are aged 17,5–18 years, Dutch-speaking, with a planned transfer to adult care in the near term. Patients with severe mental, cognitive, and/or neurological impairments are excluded. At UZ Ghent, only type 1 diabetes patients will be included, while at UZA, patient with asthma and obesity patients will be included.

Based on reference data from previous studies, the intervention target was defined as an improvement in the primary outcome corresponding to a one standard deviation (SD) increase in the TRAQ score [24–26]. This target was set assuming 90% power, an effect size of d < 0.6, and a significance level of α = 0.05. A power analysis conducted using G*Power 3.0 indicated that 22 participants per group (intervention and control) would be required. Considering the heterogeneity of the AYA population and comparable disease complexity across subgroups, this sample size was applied at the population level, resulting in a total required sample of 44 participants. To account for an anticipated attrition rate of 25% over a 24-month follow-up period [27], as well as potential recruitment challenges, the total target sample size was increased to 55 participants. Accordingly, a minimum of 28 participants per group (intervention and control) should be recruited.

For the process evaluation, all participating AYAs, their families, and involved healthcare providers will be invited to complete quantitative assessments. A purposive subsample will be selected for qualitative evaluation to capture variability in experiences and perspectives, ensuring representation across conditions, sites, and roles in the care process.

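### For effect on outcomes, the design cannot assess consistency across conditions: diabetes is inseparable from hospital, and condition-level estimates are too imprecise

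*Protocol article*

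**What the plan says.** The Discussion presents the mix of conditions as something the study contributes: "Including multiple conditions enables assessment of whether the TP performs consistently across different clinical contexts". The same sentence adds that this makes the findings more generalisable and scalable.

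Section 2.3.2 fixes who is recruited and where. "The study will focus on three common chronic childhood-onset conditions: type 1 diabetes, asthma, and obesity", and "At UZ Ghent, only type 1 diabetes patients will be included, while at UZA, patient with asthma and obesity patients will be included". No condition is recruited at both hospitals.

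The same section sizes the study. The target is an "improvement in the primary outcome corresponding to a one standard deviation (SD) increase in the TRAQ score". The power analysis "indicated that 22 participants per group (intervention and control) would be required", and "this sample size was applied at the population level, resulting in a total required sample of 44 participants". After the attrition allowance, "a minimum of 28 participants per group (intervention and control) should be recruited". No number or quota per condition is given.

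Section 2.5.1 keeps the comparison of the two groups descriptive and exploratory and describes no analysis by condition. The Discussion follows its consistency sentence with a general caution about the feasibility nature of the study. Its limitations paragraph says that several centres and conditions may make interpretation harder, but counts this heterogeneity as a strength for external validity. Nowhere does the article say that diabetes and hospital cannot be separated.

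**The concern.** To assess whether a programme works consistently across conditions, a study must be able to attribute a difference in effect to condition, and must estimate each effect precisely enough for agreement or disagreement to mean something. The recruitment rule defeats the first for diabetes against the other two conditions. The pooled sample size defeats the second for every pair of conditions.

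The practical risk is a misreading in either direction. Similar condition-level results could be taken to mean that the programme works across conditions, when the data could hardly have shown otherwise. A visible difference could be credited to condition when it belongs to the hospital. The Discussion says the results are meant to guide a larger trial and to inform policy, so such a reading would carry forward.

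**Working it through.** **Structure.** By section 2.3.2, UZ Ghent contributes diabetes only and UZA contributes asthma and obesity only. Three contrasts follow.
- Diabetes versus asthma, and diabetes versus obesity: each is also Ghent versus UZA. No sample size or model separates the two explanations.
- Asthma versus obesity: both at UZA, so not confounded with hospital.
- Intervention versus control within one condition: both groups come from the same hospital, so not confounded with hospital.

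**The plan's own sample size.** With a 1 SD effect, 90% power and two-sided α = 0.05, n per group = 2 × (1.960 + 1.282)² / 1² = 21.01, rounded up to 22. This reproduces the stated figure (the exact t calculation gives 23; power at 22 is 0.8997). The 22 does not follow from the d < 0.6 in the same paragraph, since d = 0.6 needs 59 per group by the same formula. The 1 SD target is therefore used below. The recruitment target follows from 22 × 1.25 = 27.5, rounded up to 28.

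**Patients per condition per group, equal split assumed.** Recruited: 28 / 3 = 9.3. After 25% attrition: 28 × 0.75 = 21, and 21 / 3 = 7. The required 22 / 3 = 7.3 falls in the same range.

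**Precision.** Outcome in SD units, with a common SD and independent patients, n per condition per group:
- Effect within one condition: half-width = t(0.975, 2n − 2) × √(2/n).
- Difference in effect between two conditions: half-width = t(0.975, 4n − 4) × √(4/n).

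| n | Half-width, one condition | Half-width, difference of two effects | Power for a 1 SD difference in effect |
|---|---|---|---|
| 7 | 2.179 × 0.535 = 1.16 SD | 2.064 × 0.756 = 1.56 SD | 25% |
| 8 | 1.07 SD | 1.45 SD | 28% |
| 9 | 2.120 × 0.471 = 1.00 SD | 2.037 × 0.667 = 1.36 SD | 31% |

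Power is from the noncentral t distribution with noncentrality 1/√(4/n). A 1 SD difference in effect means that one condition gets the full target benefit and the other gets none. Detecting it with 90% power would take about 43 patients per condition per group.

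Baseline TRAQ cannot be used to tighten these between-group figures, because section 2.3.1 gives controls no T0 assessment.

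**Unequal splits of 28 per group.** With 14/7/7, the half-widths within a condition are 0.78, 1.16 and 1.16 SD. With 18/6/4, they are 0.68, 1.29 and 1.73 SD. The largest condition gains and the smaller ones lose.

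**Ghent versus UZA.** With 9 versus 19 per group, or 14 versus 14, the half-width for the difference in effect is 1.15 or 1.07 SD. Even pooled by hospital, the interval is wider than the target on each side, and this is the contrast that cannot be interpreted.

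**The case against.** The strongest reply is that the article already takes a modest stance. Group comparisons are exploratory, effect sizes and intervals are emphasised over tests, and the sentence after the claim warns against definitive conclusions on effectiveness. This stands as far as it goes. But the caution is general: it does not withdraw the consistency and generalisability claim, and it does not mention the tie between condition and hospital.

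A second reply is that performance may mean delivery. Section 2.4.3 plans two observations per condition at each of three key moments (2 × 3 × 3 = 18), plus interviews with intervention-group patients covering all three diagnoses. These can describe delivery by condition. They cannot show consistency of effect, and each condition is still seen at one hospital only.

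Four stronger readings are tempting, and the documents do not support them:
- *That the whole claim is undeliverable.* The process evaluation can serve the delivery part.
- *That every comparison across conditions is confounded with hospital.* Asthma versus obesity is not, and neither is the group effect within a condition.
- *That a planned subgroup analysis lacks power.* None is planned. The power figures only measure what the claim would require.
- *That condition is known to be unbalanced between the groups.* Section 2.3.3 allocates by age and no balance by condition is stated, so imbalance is possible, but nothing shows it.

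**Conclusion.** The point holds for effect on outcomes. That diabetes and hospital are inseparable follows directly from the recruitment rule and needs no assumption. The imprecision rests on an equal split over the three conditions, a common SD, and the plan's own numbers and attrition rate. Under these, an interval for the difference in effect between two conditions extends further on each side than the whole target effect. Departing from the equal split does not rescue the claim, because it makes the smaller conditions less precise.

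No sample size, primary estimate or planned test depends on the sentence. What needs correcting is a property claimed for the design, together with a limitation that is not stated.

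**What to change.** 1. Reword the sentence in the Discussion. Condition-specific effects will be shown descriptively with confidence intervals, no conclusion on consistency of effect across conditions will be drawn, and consistency of delivery will be described only through the process evaluation. The generalisability and scalability wording should be softened to match.
2. Add to the limitations paragraph that condition and hospital are confounded for diabetes versus asthma and obesity.
3. Because allocation is by age with no stated balance by condition, include condition as a stratum or adjustment term in the exploratory pooled between-group estimate. Condition carries hospital with it. Keep it also if propensity weighting proves infeasible, a possibility that section 2.5.1 leaves open.

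The cost is a few sentences, a weaker stated claim, and up to two degrees of freedom. Recruitment is not affected. Data collection runs to December 2026, so the change can be made before results are known.

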## Abbreviations

AYA: Adolescent and young adult
TP: Transition programme
EBCD: Experience-based co-design
QALY: Quality-adjusted life year
ICER: Incremental cost-effectiveness ratio
